### Study objectives

This study examines the efficacy, safety and cost-effectiveness of nabiximols in the outpatient treatment of cannabis dependent treatment seeking patients who have not previously responded to conventional psychosocial interventions. Specific study objectives are:Primary Objective 1: To examine the effects of nabiximols vs. placebo on a range of cannabis treatment efficacy outcomes, primarily, changes in illicit cannabis use during treatment and effects on retention in treatment.Primary Objective 2: To examine the adverse event profile and abuse liability of nabiximols as a take home treatment for cannabis use disorder.Primary Objective 3: To assess the costs and health related quality of life (HRQoL) associated with nabiximols treatment and the potential societal savings (decreased health care, improved productivity, and decreased criminal behaviours).Secondary objectives: To examine changes in health related outcomes during outpatient treatment with nabiximols, including a range of mental and physical health dimensions, cognitive function, and psychosocial functioning.

## Methods

### Study design

This project is a phase III multisite (four-sites) outpatient randomised double-blind placebo controlled parallel design comparing a 12-week course of buccally administered nabiximols to placebo (Fig. 1). Both groups receive structured ‘best practice’ individual counselling based on cognitive behavioural therapy principles, regular case management and clinical reviews over the course of the trial. Medications (nabiximols, placebo) are dispensed on a weekly basis, and study medication is discontinued in week 12 using tapering doses. Participants are followed up at week 24, 12 weeks after discontinuation of nabiximols/placebo treatment. All participants are also followed-up for confidential research interviews, (irrespective of completion of the trial intervention) at baseline (week 0), weeks 4, 8, 12 and 24. Overview of study procedures and sequence of events is provided in Table 1.

**Fig. 1 Fig1:**
[figure not shown]
Overview of study design

**Table 1 Tab1:** Table of schedule of events

	Study period															
	Screen	Enrol	Post-allocation													Follow up
Timepoint*	-t_1_	0	Wk 1	Wk2	Wk3	Wk4	Wk5	Wk6	Wk7	Wk8	Wk9	Wk 10	Wk 11	Wk 12	Wk 13	Wk 24
Enrolment																
Phone screen (Eligibility)	X															
Informed consent for medical screen	X															
Medical screen/assessment (Eligibility)	X															
Informed consent for main study participation		X														
Allocation		X														
Intervention																
Medication *[Nabiximols or placebo]* dispensed			X	X	X	X	X	X	X	X	X	X	X	X	X	
*Nursing clinical reviews*			X	X	X	X	X	X	X	X	X	X	X	X	X	
*Medical clinical reviews*			X	X		X				X				X		
*CBT sessions*				X		X		X		X		X		X		
*Urine drug screen*		X	X	X	X	X	X	X	X	X	X	X	X	X		X
Assessments																
Research Interviews. Variables include: Cannabis & other substance use (TLFB), CWS, AEs, Aberrant medication behaviour (mod ORBIT), SF-6D (QOL), WHO Health and Performance Questionnaire: CT version, SF-36 (Physical and Mental health), DASS-21, PHQ-15, OTI: BPI, Crime, Satisfaction, Test blind (week 12 only)		X				X				X				X		X
Clinical (Nursing/medical) Review variables: AEs, Aberrant medication behaviour (weigh bottles), ratings dose adequacy, ATOP & BPRS at 4 week intervals, reason for study termination Wk 24.			X	X	X	X	X	X	X	X	X	X	X	X		
Cognitive assessment. Variables include Blood samples (pre/post cognitive testing), Cognitive testing, Abuse liability (subjective liking, strength, Physiological response)		X				X										X

### Regulatory and funding

The design complies with requirements of the Consolidated Standards of Reporting Trials (CONSORT) guideline [31, 32] (see Additional file 1 for SPIRIT CONSORT checklist), and has received ethical clearance from the Human Research Ethics Committee of South East Sydney Local Health District (HREC/14/POWH/701), with relevant local site specific approvals. The University of Sydney is the study sponsor. A National Health and Medical Research Council (NHMRC) of Australia Project Grant (#1088902) supports the research costs of the study. Health service costs are predominately supported by the participating NSW Health services. Study medications (nabiximols, placebo) are provided free to the study by GW Pharmaceuticals. The study is registered on the Australian New Zealand Clinical Trials Registry (ACTRN12616000103460).

A Data Safety Monitoring Board (DSMB) comprising of an independent statistician, a researcher with cannabinoid expertise, and an addiction medicine specialist with extensive expertise in clinical trials oversees the study.

### Sites

Four clinical sites across three Local Health Districts in New South Wales, Australia were selected to host the study based on their location, history of providing specialist treatment services for cannabis dependent users, and capacity to participate and co-ordinate clinical research activities. Two clinical sites are based in the South East Sydney Local Health District (The Langton Centre and St George Hospital), one in Hunter New England Local Health District (Newcastle Community Health Services) and one in Western Sydney Local Health District (Centre for Addiction Medicine).

### Participants

#### Sample size

Based on the primary outcome measure (efficacy, safety and cost-effectiveness of nabiximols in outpatient treatment of cannabis dependence), a total sample size of 142 participants (71 per group) is required to achieve around 22% abstinence rates at 12-weeks for the placebo group (ascertained by average of previous drug administered clinical trials) and approximately 44% abstinence rates for the nabiximols group (based on clinical judgement of double the rate of abstinence than placebo) with 80% power (two-tailed) and α = 0.05.

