### Randomisation and blinding

An independent statistician created a randomisation schedule, which was then given to the lead trial pharmacist at each site. Participants are blindly randomised in a 1:1 ratio between groups, using the variable 8-block randomisation schedule of 80 codes per site to maintain blinding. Stratification occurs at each of the four sites (aiming for a 1:1 random allocation at each site). Randomisation and group allocation happen after enrolment (informed consent) and prior to Day 1 of the study, enabling study medications to be prepared by the study pharmacist at each site. The randomisation schedule and nabiximols and placebo canisters are only identifiable to trial pharmacists at each site, who themselves have no contact with participants. All participants, clinicians and researchers involved in service delivery, data collection and analysis remain blinded to group allocation (active or placebo) until the end of the study.

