	Rey Auditory Verbal Learning Task [62]	Retention of a 15 item word list presented on 5 occasions. Number of words recalled on each presentation, following presentation of a novel list of 15 words; and then after brief and long delays recorded. Recognition of target stimuli also assessed.	Research Interview: Weeks 0, 4, 24

#### Objective 1

To examine cannabis treatment efficacy outcomes, including changes in illicit cannabis use during treatment and treatment retention.Illicit cannabis use is quantified as self-reported number of days of illicit cannabis use and average daily amount of cannabis use in grams at the 4 weekly research interviews using modified Timeline Followback [40] techniques. The primary end-point is self-reported illicit cannabis use days during the maintenance phase of treatment (weeks 1-12). Objective measures of illicit cannabis use will be determined from weekly urine collection with quantitative analysis of urinary THC, THC-COOH, CBD and other cannabinoids. 4-weekly point prevalence abstinence during maintenance phase (weeks 1-4, 5-8, 9-12), and post-treatment period (week 24) will be ascertained by combining self-report data from researcher interviews and urinalysis.Treatment retention (days in protocol treatment) are recorded from clinical records. Participants who do not attend for more than two consecutive weeks are deemed to have dropped out of treatment, and the last scheduled day of dosing is calculated as the end of treatment date.

#### Objective 2

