## Statistical analyses

Chi square and ANOVA tests will be performed to identify any baseline covariates that differ between groups. Prior to carrying out primary and secondary analysis, the percentage of missing values in the raw dataset and Little’s MCAR test will be used to determine if multiple imputation of missing values is required (except for missing urine where cannabis use will be assumed to have taken place). The multiple imputation will be done if the percentage of missing values exceeds 5%.

All analyses will use Intention-to-treat, which is defined as any person who is randomised to one of the study arms and receives at least one dose of study medications. Mixed Models for Repeated Measures (MMRM) will compare groups on changes in outcome variables (cannabis use and secondary outcomes) in the medication phase with the multiply imputed dataset, (assuming that Little’s MCAR at Random test confirms the data to be missing at random). In addition, we will perform a sensitivity analysis based on only those with complete data, and compare results to that from the MI dataset analysis.

Adverse Events will be analysed using chi-square. A Cox proportional hazards model will compare retention in treatment between study arms, controlling for potential confounds. The impact of the intervention on post-medication outcomes will compare changes in cannabis use outcomes at baseline and at follow up between groups using MMRMs.

Family-wise error corrections will control for Type 1 errors where multiple comparisons are performed within a particular analysis where post hoc contrasts are performed to further explore interesting (significant) findings.

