## Study limitations

This study has a number of possible limitations. One issue relates to retention in study protocol. Participation in the study is voluntary, and study procedures span 24 weeks, including 13 weeks of study treatment interventions. The lengthy treatment duration in the study is generally longer than conventional treatment of cannabis dependence, and participants may be deterred from entering the trial or prematurely terminate study participation, which in turn may have implications in assessing effectiveness of treatment outcomes and research follow-up. Similarly, individuals enrolling in a medication study may have different levels of interest or commitment to the CBT in the study, which may enhance heterogeneity of outcomes.

The study uses a flexible dosing approach to medication. Whilst a fixed regimen – or indeed a structured comparison of different doses (e.g. high or low) is often used in many medication studies – experience from opioid agonist clinical and research practice highlights the need to tailor doses to individual requirements, reflecting differing physiological tolerance, adverse event profiles and behavioural characteristics of patients. Nevertheless, the different doses used may increase heterogeneity of outcomes and limit the ability to detect significant differences if there is indeed a major dose effect.

Measures of illicit cannabis use during treatment are the primary study outcome, with self-reported use (via the TLFB) as the primary endpoint. Participants may have a response bias and report inaccurate drug use to both clinicians and researchers. Whilst objective assessment of illicit cannabis use using urine drug screening should enhance self-report validity, it remains to be seen whether illicit cannabis use can be differentiated from prescribed nabiximols use. Various toxicological approaches are being examined to validate the identification of illicit cannabis use in nabiximols prescribed patients (to be described elsewhere).

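### The stated 80% power is for 12-week abstinence, not for the declared primary endpoint of self-reported use days, for which no power or detectable difference is given

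*Protocol article*

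**What the plan says.** The Sample size section opens "Based on the primary outcome measure (efficacy, safety and cost-effectiveness of nabiximols in outpatient treatment of cannabis dependence" and continues that "a total sample size of 142 participants (71 per group) is required to achieve around 22% abstinence rates at 12-weeks for the placebo group". The other inputs are about 44% for nabiximols (twice the placebo rate, by clinical judgement), 80% power and a two-sided alpha of 0.05. The placebo rate is described as an average from earlier drug trials.

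Under Objective 1 of the outcome measures, the article states: "The primary end-point is self-reported illicit cannabis use days during the maintenance phase of treatment (weeks 1-12". Study limitations repeats this, "with self-reported use (via the TLFB) as the primary endpoint". Objective 1 treats abstinence separately, as 4-weekly point prevalence that combines self-report with urinalysis. The Abstract lists several primary endpoints, and a 12-week abstinence proportion is not among them.

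The Statistical analyses section says that "Mixed Models for Repeated Measures (MMRM) will compare groups on changes in outcome variables", cannabis use included, on multiply imputed data where imputation is needed. Missing urines are taken as cannabis use. No section gives an expected difference in use days, its standard deviation, a within-person correlation, a power for use days or an expected rate of loss.

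**The concern.** The power statement says that it rests on the primary outcome measure, but the outcome it uses is not the declared primary endpoint. The two differ in scale (a proportion against a number of days), in time frame (week 12 against weeks 1-12) and in analysis (two proportions against MMRM). If the abstinence of Objective 1 is meant, they also differ in data source. The label in the Sample size section joins efficacy, safety and cost-effectiveness. That is a set of study aims, not an outcome that can be sized, and it matches neither endpoint.

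A reader will attach the 80% to the primary result. If use days then show no clear difference, there is no planned detectable effect to compare the result with. The mismatch also leaves it less clear whether use days or abstinence was meant to carry the confirmatory claim. A second, smaller question is whether the 80% holds even for abstinence once patients are lost, since no loss allowance is mentioned.

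**Working it through.** **1. Reproducing the 142.** Inputs from the Sample size section: p1 = 0.22, p2 = 0.44, two-sided alpha 0.05 (z = 1.960), power 80% (z = 0.842). Allocation is equal (Randomisation and blinding: "Participants are blindly randomised in a 1:1 ratio between groups"). The pooled proportion is (0.22 + 0.44)/2 = 0.33.

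n per arm = [z(0.975)·√(2·p̄(1−p̄)) + z(0.80)·√(p1(1−p1) + p2(1−p2))]² / (p2 − p1)²

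= [1.960 × 0.6650 + 0.842 × 0.6465]² / 0.22² = (1.3033 + 0.5441)² / 0.0484 = 70.5, rounded up to **71 per arm, 142 in total**.

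Power at 71 per arm: Φ[(√71 × 0.22 − 1.3033)/0.6465] = Φ(0.851) = **80.3%**.

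The formula matches exactly with no inflation. It is therefore a calculation for two abstinence proportions, and nothing was visibly added for losses.

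**2. Abstinence power under losses.** The article gives no loss rate, so 10%, 20% and 30% are assumptions. There are three readings of the 22% and 44%:

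| Missing | Rates already count missing as use | Losses excluded (n = 71 × (1−d)) | Rates hold in patients with data, missing then counted as use (rates × (1−d), n = 71) |
|---|---|---|---|
| 10% | 80% | 76% (n = 63.9) | 74% (19.8% vs 39.6%) |
| 20% | 80% | 71% (n = 56.8) | 67% (17.6% vs 35.2%) |
| 30% | 80% | 65% (n = 49.7) | 59% (15.4% vs 30.8%) |

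The article does not say which reading applies.

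**3. Use days.** Power for the planned MMRM cannot be computed, because the article gives none of the inputs. As an illustration only, a simple two-sample comparison of means (t-test, two-sided 0.05, 80% power) detects these standardised differences:

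- 71 per arm: 0.47
- 57 per arm (about 20% loss): 0.53
- 50 per arm (about 30% loss): 0.57

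In days out of 84 (12 weeks × 7), with 71 per arm and an assumed SD of 15, 20, 25, 30 or 35 days, the detectable difference is the SD × 0.473, or about 7, 9, 12, 14 or 17 days. With 50 per arm (SD × 0.566) it is about 8, 11, 14, 17 or 20 days. The SDs are assumptions.

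**The case against.** Four points can be made for the plan.

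First, abstinence is not a stray outcome. It sits under Objective 1, and Study limitations calls measures of illicit cannabis use the primary study outcome, so the sizing used a related measure from the same domain. That stands as context. It does not make abstinence the declared endpoint, which is named twice as self-reported use.

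Second, an article may leave an SD, a correlation or an attrition rate to the full protocol or the analysis plan. That also stands, and their absence alone would be no finding. The fault is that the article ties its power to the primary outcome measure and names a different primary endpoint.

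Third, a reader might infer that the primary analysis is underpowered. The documents do not support this. A repeated-measures analysis of days can have more or less power than a test of two proportions, and the inputs to decide are absent. The figures of 0.47 to 0.57 come from a t-test that drops whole patients, whereas MMRM with imputation keeps partial data.

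Fourth, a reader might infer that the 80% for abstinence holds only with 142 fully evaluable patients. That is not shown. If the earlier trials counted dropouts as users, losses are already inside the 22%. Study limitations raises early termination as a possibility and gives no rate. The Study design section has research interviews continue whether or not treatment is completed, so stopping treatment need not mean losing use-days data.

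**Conclusion.** The concern holds as an endpoint mismatch. The 142 is arithmetically right for 22% vs 44% abstinence, and the 80% (80.3%) applies to that comparison. It does not apply to self-reported use days over weeks 1-12, for which the article states neither power nor a detectable difference. Whether the primary analysis has enough power is unknown from this document.

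The point about losses is conditional. At 30% missing, abstinence power runs from 59% to 80%, depending on how the 22% and 44% treat missing patients and on whether losses are excluded or counted as use. The loss rates are assumptions.

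This should be fixed, because a stated power is attached to the wrong endpoint. It does not call the trial size, the endpoint or the analysis into question.

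**What to change.** Keep 142 and rewrite the Sample size paragraph:

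- **(a)** Label the 22% vs 44% calculation as power for 12-week abstinence. State whether those rates already count missing patients as users. If they do not, restate the power with an expected loss.
- **(b)** Remove efficacy, safety and cost-effectiveness as the sizing outcome, and name self-reported use days over weeks 1-12 as the primary endpoint.
- **(c)** Give the difference in use days detectable with 71 per arm under the planned model, with a stated SD, within-person correlation and loss. Alternatively, say plainly that the trial was sized on abstinence and that no power is claimed for use days.

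The cost is one reworded paragraph and at most one recalculation, with no extra patients and no change to endpoint or analysis. The stated abstinence power may become less favourable.

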#### Eligibility criteria

Inclusion criteria are: (a) age 18 to 65 years; (b) meet ICD-10 cannabis dependence criteria; (c) inability to stop cannabis use in previous attempts, operationalised as relapse to cannabis use within one month of a substantive cessation attempt (including prior episodes of counselling, medication, or withdrawal treatment aimed at abstaining from cannabis use), and (d) being willing and able to provide informed consent and follow study procedures, including agreeing to not drive or operate heavy machinery and females of child bearing potential agree to use reliable contraception during the duration of the trial.

#### Exclusion criteria

Exclusion criteria for the study are: (a) presence of another substance use disorder other than nicotine or caffeine (i.e. alcohol, other illicit or prescription drug dependence, including methadone or buprenorphine treatment for opioid dependence); (b) severe medical (e.g. severe chronic pain, severe hepatic, cardiovascular or renal impairment) or psychiatric disorder (e.g. unstable schizophrenia, recent drug-induced psychosis, severe mood disorder), assessed at medical screen; (c) women who are pregnant, lactating or planning to become pregnant; (d) concerns regarding safe storage of medication; (e) not available for follow up (e.g. expected travel or incarceration); (f) mandated by court to attend treatment and maintain abstinence for a substance use disorder; (g) history of epilepsy or recurrent seizures; and (i) current active or recent (within past month) treatment for cannabis use disorder.

#### Early termination criteria

Early termination criteria for the study include: (i) severe adverse side effects or deteriorating physical or mental health; (ii) violation of treatment centre rules and conditions (e.g. violence towards staff or other patients); (iii) non-compliance with trial protocol, including missing/not returning medication for more than two consecutive weeks or persistent refusal to participate in trial procedures (such as, non-adherence with study medications, counselling, clinical reviews, case management urine drug screen, bloods, research interviews or monitoring).

### Recruitment

The study is promoted via; (i) referrals from Drug & Alcohol treatment services; (ii) media advertising, including local newspapers and postcard placements; and (iii) online advertising through University of Sydney website.

A three-step recruitment procedure is used for the study. Interested individuals contact either the central trial coordinator or site-specific researchers by telephone, and are screened for potential eligibility. Information collected at telephone screen relate to the selection criteria, including demographics; recent cannabis and other substance use in past 28 days, Cannabis Severity of Dependence Scale (SDS) score [33]; participation in treatment for substance use disorder in last 28 days; self-reported severe mental and physical health conditions; prior quit attempts; willingness and ability to participate in the study, including weekly clinic attendance. If deemed broadly eligible at telephone screen, the potential participant is invited to attend a detailed medical assessment with a study medical officer at one of the four sites, generally within 1-2 weeks of the telephone screen.

The medical assessment is conducted by a study medical officer (SMO) - an Addiction Medicine Specialist or delegated senior addiction medicine trainee, and involves a comprehensive clinical assessment examining patient goals, substance use and treatment history, physical and mental health, and psychosocial conditions. In addition to the physical and mental state examinations, clinical investigations, such as, urine drug screen for cannabis and other substance use, urine β-hCG in women to exclude pregnancy, and blood tests are carried out as clinically indicated (e.g. Liver Function Tests if concerned regarding hepatic function). The SMO completes the eligibility checklist following the assessment, and if the patient is eligible and interested in participating in the study, they are referred to the study researcher at each site.

The researcher then provides detailed verbal and written study information, and obtains written informed consent to participate in the study. Upon signing the informed consent form, participants are enrolled into the study.

